### Recruitment

Recruitment will take place sequentially at the four participating HD units. From pilot data, we anticipate that approximately 20% of the 400 HD patients in participating units will meet the criteria for IDH [38] and at least half of the eligible participants (40 participants) will be willing to participate in our study [50, 51].

### Assignment of intervention, allocation concealment mechanism and implementation

Randomization of allocation sequence will be done using computer-generated random numbers under the supervision of a statistician in the Department of Medicine, University of Calgary. Subsequently, the allocation sequence will be inserted into sequentially numbered, opaque, sealed envelopes. Following study consent and enrollment, an envelope containing the allocation sequence will be provided to the patient’s HD nurse, who will implement the intervention according to the protocol.

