## Methods/Design

### Study design

This is a 22-week parallel-group randomized crossover trial. During the first part of the study, the run-in and dialysis optimization phase, eligible participants will undergo a 4-week run-in. During this period, all participants will undergo a comprehensive clinical assessment including a clinical weight assessment, an antihypertensive medication review and standardization of their dialysis prescription. At the end of the run-in phase, participants that still meet the eligibility criteria will enter part 2, the randomized crossover phase. In this phase, the participants are randomized to regular best clinical practice HD (without BVM-guided UF biofeedback; the control arm) or to best clinical practice plus BVM-guided UF biofeedback (the intervention arm) for an 8-week period. This will be followed by a 2-week washout phase and then the participants will be crossed over for a second 8-week phase. The participant flow chart and timeline are shown in Figure 1. The study will be conducted and reported following the Consolidated Standards of Reporting Trials (CONSORT) 2010 guidelines [35]. The study protocol was approved by the University of Calgary Conjoint Health Research Ethics Board (ethics ID: REB13-1139).

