### Interventions

#### Part 1: run-in phase

Following enrollment, participants will undergo a 4-week run-in phase to optimize their dialysis weight and dialysis prescriptions, and to determine the critical relative blood volume values (BVM will be enabled). During the first 2 weeks of the run-in phase, participants will undergo a medication review and dry-weight reduction based on a modified protocol from the Dry-Weight Reduction In Hypertensive Hemodialysis Patient (DRIP) trial [37, 38].

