#### Part 2: crossover study phase

Participants that continue to have more than 30% of their sessions complicated by symptomatic IDH during the run-in phase are randomized to either 8 weeks of best clinical practice (without BVM or biofeedback; control) or best clinical practice plus BVM-guided UF biofeedback (intervention), followed by a 2-week washout period (using the control phase HD prescription) before crossing over to the other study arm for a second 8-week block. Participants will have clinical assessments of their dry weight at the beginning of each week.

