### Data collection

#### Collection of baseline and run-in phase data

Baseline patient demographics (age, gender, HD vintage and race), comorbidities (e.g. congestive heart failure, diabetes mellitus and peripheral vascular disease), cause of renal disease, medications (number and class of antihypertensive), laboratory investigations (e.g. serum electrolytes, complete blood count and albumin), HD prescription (dialyzer type, composition, temperature, blood and dialysate flow rates, target weight, anticoagulation, use of sodium and/or UF profiles), and number of episodes of IDH over the preceding 8 weeks and run-in phase will be extracted from HD charts and local electronic health records by the study investigator.

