#### Collection of primary outcome variables

Both sitting and standing blood pressure will be measured in a standardized fashion at the beginning and end of each dialysis session [52, 53]. Intradialytic blood pressures will be measured in a sitting position every 30 minutes and at the time of IDH-related symptoms as defined in the outcomes section. Sitting blood pressures will be measured with the patient seated with their feet flat on the floor or a foot rest, back against a chair with a bare arm resting on a support, whereby the midpoint of the upper arm is at the level of the heart. Standing blood pressures will be measured with the patient standing feet flat on the floor, with a bare arm resting on a support, whereby the midpoint of the upper arm is at the level of the heart. An appropriate-sized blood pressure cuff, where the cuff bladder length is 80% of the arm circumference, will be used. Blood pressure taken while the patient is in a Trendelenburg or supine position will be accepted if the patient is unable to sit during the pre-specified blood pressure measurement or is experiencing IDH-related symptoms. All blood pressures will be measured using an automated cuff attached to the dialysis machine. Manual blood pressure will be accepted if an automated blood pressure measurement cannot be obtained. Blood pressure, method of measurement, patient position, IDH-related symptoms and nursing interventions will be recorded by the bedside dialysis nurse.

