### Ethics

Ethical approval has been granted from the University of Calgary Research Ethics Board. The research coordinator will determine patient eligibility, obtain consent from participants for participation in the study and access the sealed envelope containing allocation details. The coordinator will obtain the HD run sheets and submit them to an independent data entry clerk who is blinded to allocation. All data are kept strictly confidential. The principal investigator (JM) and study personnel (KL) are responsible for coordination of the study. The trial is registered with Clinicaltrials.gov (NCT01988181).

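### The stated trigger for releasing the allocation envelope comes before the run-in that settles final eligibility, so the text does not protect concealment until the point of randomization

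*Protocol article*

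**What the plan says.** All references are to the Protocol article.

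- **Envelope release** (Assignment of intervention, allocation concealment mechanism and implementation): "Following study consent and enrollment, an envelope containing the allocation sequence will be provided". The named recipient is the HD nurse caring for that participant. The envelopes are sequentially numbered, opaque and sealed, and the nurse then carries out the allocated treatment.
- **Enrolment** (Part 1: run-in phase): "Following enrollment, participants will undergo a 4-week run-in phase".
- **Randomization** (Part 2: crossover study phase) has this rule: "Participants that continue to have more than 30% of their sessions complicated by symptomatic IDH during the run-in phase are randomized". Study design agrees: "At the end of the run-in phase, participants that still meet the eligibility criteria will enter part 2, the randomized crossover phase". Table 1 puts randomization between the mid-week 4 and mid-week 8 columns.
- **Recording of the events** (Collection of primary outcome variables): "IDH-related symptoms and nursing interventions will be recorded by the bedside dialysis nurse".
- **Extraction of the run-in count** (Collection of baseline and run-in phase data): the IDH count, both for the 8 weeks before the study and for the run-in, is covered by this rule: "run-in phase will be extracted from HD charts and local electronic health records by the study investigator".
- **Eligibility and envelope** (Ethics): the research coordinator determines eligibility, obtains consent and is also to "access the sealed envelope containing allocation details".

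**The concern.** Sealed envelopes conceal allocation only if they stay shut until the decision to randomize is final. Here that decision falls at the end of the run-in and depends on how many sessions were recorded as symptomatic IDH. The only trigger given for releasing the envelope, consent and enrolment, lies four weeks earlier. The named recipient is the person who records the symptoms that feed the count, and the protocol itself (Secondary outcomes) calls IDH-related symptoms subjective. The other person named as handling the envelope is the one who determines eligibility.

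If an allocation were seen before requalification was settled, a borderline participant could be recorded into or out of the randomized phase according to the order of treatments that was coming. The two sequence groups would then no longer be a purely random split.

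**Working it through.** The plan states no figure on this point, so there is nothing to reproduce. The check has two parts.

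**1. Order of events**

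| Event | When, as stated | Section |
|---|---|---|
| Consent and enrolment | Before the run-in | Part 1: run-in phase |
| Envelope to the HD nurse | After consent and enrolment; no later condition | Assignment of intervention |
| Run-in, IDH recorded by the bedside nurse | Weeks 1-4 | Part 1; Collection of primary outcome variables |
| Requalification (>30% of sessions) | End of run-in | Study design; Part 2 |
| Randomization | After run-in, if requalified | Study design; Part 2; Table 1 |
| Coordinator accesses the envelope | No time given | Ethics |

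The envelope's trigger sits above the requalification step, and no section holds the envelope back until that step is done. The text therefore permits early release. It does not require it, and no section says an envelope is opened in weeks 1-4.

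**2. How often one recorded session could decide entry (illustration)**

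Inputs from the documents: 3 to 4 sessions per week (Study participants), a 4-week run-in and a threshold of more than 30%.

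- 3 per week: n = 3 × 4 = 12; 0.30 × 12 = 3.6, so at least r = 4 sessions are needed.
- 4 per week: n = 4 × 4 = 16; 0.30 × 16 = 4.8, so at least r = 5 sessions are needed.

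Assumptions not in the documents: sessions are independent, and the true per-session probability p of symptomatic IDH lies between 0.20 and 0.40.

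The chance of ending exactly one session short is P(X = r − 1) = C(n, r − 1) p^(r−1) (1 − p)^(n−r+1). The chance of ending exactly at the threshold is P(X = r).

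| p | n = 12: one short (3) | n = 12: at threshold (4) | n = 16: one short (4) | n = 16: at threshold (5) |
|---|---|---|---|---|
| 0.20 | 0.236 | 0.133 | 0.200 | 0.120 |
| 0.25 | 0.258 | 0.194 | 0.225 | 0.180 |
| 0.30 | 0.240 | 0.231 | 0.204 | 0.210 |
| 0.35 | 0.195 | 0.237 | 0.155 | 0.201 |
| 0.40 | 0.142 | 0.213 | 0.101 | 0.162 |

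For example, at n = 12 and p = 0.25: 220 × 0.25³ × 0.75⁹ = 0.258.

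Over this range the chance of being exactly one session short is about 0.14-0.26 with 12 sessions and 0.10-0.23 with 16. This shows how many participants could sit where one entry matters. It does not show how often an entry would be altered, or by how much the rate ratio would move.

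**The case against.** **A consistent reading exists.** *Following* sets only an earliest time. The nurse is given the envelope in order to deliver the allocated treatment, which first happens in Part 2, and three places put randomization after the run-in. The Sample size section enrols 34 to cover dropout without mentioning run-in failures, so enrolment may there mean entry to the randomized phase. This stands as a possible reading, and it is why the point is about what the text permits. But the run-in section explicitly puts enrolment first, and no section supplies the missing condition.

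**A reader might infer that the nurse knows the order while recording run-in symptoms.** The documents do not support that. The envelopes are opaque and sealed, so holding one is not knowing its content. The Blinding section's statement that the nurse is unblinded rests on the machine's biofeedback screens, prompts and alarms. The nurse also does not decide entry: the investigator extracts the count and the coordinator determines eligibility. The count is, however, drawn from records of what the nurse wrote down.

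**A reader might also infer that envelopes used on run-in failures would systematically unbalance the two orders.** That does not follow. Losses unrelated to the allocation add chance imbalance only.

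**The two handlers can be partly reconciled.** The coordinator could take the envelope and pass it to the nurse. That is plausible, but it is not stated, and it leaves open who opens it and when.

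**The crossover limits the harm.** Every participant is due to receive both treatments and serves as their own control. This stands, and it narrows the risk to who enters which order.

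**A condensed article may leave envelope custody to the full protocol.** That would answer an omission. Here the article does state a trigger, and the trigger conflicts with its own point of randomization.

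**Conclusion.** The concern holds as an inconsistency in timing and handling. The release rule as written precedes the final eligibility test, and two sections name different handlers, each with a part in establishing eligibility. The text thus allows allocation to be exposed before requalification is settled; it does not show that this happens. The consequence at risk is selective entry by treatment order, not selection for whether biofeedback is ever received. The one-session-short probabilities rest on assumed independence and assumed IDH rates, and they indicate opportunity only; bias in the rate ratio is not quantified. It should be fixed, because the correction protects concealment at almost no cost.

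**What to change.** In the section on assignment and allocation concealment, replace the enrolment trigger with a statement that the next numbered envelope is opened only after the run-in has ended and requalification on the >30% criterion has been recorded and locked. Name the one role that opens it. Amend the Ethics section so that it names the same role at the same time, and says how the allocation then passes to the nurse who delivers it.

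Cost: wording in two sections and a short site instruction. No additional visits, staff or data are needed.

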### Blinding

Given the nature of our intervention, and the inability to disable the BVM-guided UF biofeedback screens, prompts and alarms, we will not be able to blind the study personnel (KL) or the bedside dialysis nurse. The trial participants will be blinded to the intervention. To reduce bias, the HD nurse will be encouraged to document all intradialytic symptoms and interventions, as well as not to reveal the allocation sequence to the trial participant. In addition, study personnel (KL) will assess target weights and administer surveys uniformly. Study personnel involved with data abstraction and analysis will be blinded to the study intervention.

### Data collection

#### Collection of baseline and run-in phase data

Baseline patient demographics (age, gender, HD vintage and race), comorbidities (e.g. congestive heart failure, diabetes mellitus and peripheral vascular disease), cause of renal disease, medications (number and class of antihypertensive), laboratory investigations (e.g. serum electrolytes, complete blood count and albumin), HD prescription (dialyzer type, composition, temperature, blood and dialysate flow rates, target weight, anticoagulation, use of sodium and/or UF profiles), and number of episodes of IDH over the preceding 8 weeks and run-in phase will be extracted from HD charts and local electronic health records by the study investigator.

#### Collection of primary outcome variables

Both sitting and standing blood pressure will be measured in a standardized fashion at the beginning and end of each dialysis session [52, 53]. Intradialytic blood pressures will be measured in a sitting position every 30 minutes and at the time of IDH-related symptoms as defined in the outcomes section. Sitting blood pressures will be measured with the patient seated with their feet flat on the floor or a foot rest, back against a chair with a bare arm resting on a support, whereby the midpoint of the upper arm is at the level of the heart. Standing blood pressures will be measured with the patient standing feet flat on the floor, with a bare arm resting on a support, whereby the midpoint of the upper arm is at the level of the heart. An appropriate-sized blood pressure cuff, where the cuff bladder length is 80% of the arm circumference, will be used. Blood pressure taken while the patient is in a Trendelenburg or supine position will be accepted if the patient is unable to sit during the pre-specified blood pressure measurement or is experiencing IDH-related symptoms. All blood pressures will be measured using an automated cuff attached to the dialysis machine. Manual blood pressure will be accepted if an automated blood pressure measurement cannot be obtained. Blood pressure, method of measurement, patient position, IDH-related symptoms and nursing interventions will be recorded by the bedside dialysis nurse.

#### Collection of secondary outcome variables

Dialysis adequacy, bioimpedance, BNP, high-sensitivity cardiac troponin, intra- and interdialytic symptom survey and antihypertensive medication use will be collected by study personnel at the pre-specified times (Table 1).

**Table 1 Tab1:** **Data collection schedule**

		Part 1			Part 2			Part 2	
	Every session	Mid-week 1	Mid-week 4		Mid-week 8	Mid-week 12		Mid-week 18	Mid-week 22
Hemodialysis run sheet	X			Randomization			Crossover and washout		
*Kt*/*V*	X								
Electrical bioimpedance		X	X		X	X		X	X
Brain natriuretic peptide		X	X		X	X		X	X
High-sensitivity cardiac troponin		X	X		X	X		X	X
Intradialytic symptom survey	X								
Interdialytic symptom survey	X								
Medication review		X	X		X	X		X	X

### Participant retention and follow-up

Following enrollment, every effort will be made to follow up participants until the end of the study phase. Participants moving to different dialysis sites across the city of Calgary will be followed unless they move to a site not using the Fresenius 5008 machines, at which point they will be censored. Participants who move out of the city will be censored.

### Statistical analysis

We will use mixed-effects Poisson regression to test the null hypothesis that the ratio of the rate of IDH episodes (main model exposure) during the intervention phase over the rate of IDH episodes during the control phase will range between 0.7 and 1.3 (i.e., the alternative two-sided hypothesis is that the incidence rate ratio will be 0.7 or lower). We will study the effect of the intervention as a fixed effect and account for the correlation in the data due to the subject using random effects. The multi-level model will have errors due to within-subject variation and due to between-cluster variation (between subject variance). In the event that the study generates over-dispersed data, we will use a negative binomial regression with the approach as described above. We will also explore whether participants with larger drops in systolic blood pressure (>30 mmHg) benefit from the planned intervention. They will be analyzed as a subgroup.

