### Sample size calculation

We have previously estimated that 23% of our HD population have IDH [38]. To estimate the sample size, we conservatively assumed that only one IDH episode would occur per run (although it is likely that more than one episode will occur per run, increasing the study power). With this approach, and using a 2 × 2 crossover design, we estimated that a sample size of 30 participants would provide a power of 90% to demonstrate a 30% reduction in the rate of IDH under the biofeedback treatment vs. the control treatment, with a two-sided alpha of 0.05. We will enroll 34 participants to guard against dropout, which can be as high as 30% [41]. These estimates are based on simulation studies assuming only one IDH episode per run and two Poisson processes with average rates of IDH equal to 7 (control) and 5 (intervention) episodes over 24 runs. We used R (R Foundation for Statistical Computing, Vienna, Austria) [49] for simulations, and the package clusterPower in R.

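### The primary null is written as a rate ratio between 0.7 and 1.3, so the effect the trial was sized on (5/7 = 0.714) lies inside the null and the stated 90% power does not apply to it

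*Protocol article*

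**What the plan says.** Protocol article, Statistical analysis: "We will use mixed-effects Poisson regression to test the null hypothesis that the ratio of the rate of IDH episodes" in the intervention phase to that in the control phase "will range between 0.7 and 1.3 (i.e., the alternative two-sided hypothesis is that the incidence rate ratio will be 0.7 or lower". Intervention is a fixed effect and subject a random effect, with negative binomial regression as the fallback if the counts are over-dispersed.

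Protocol article, Sample size calculation: for a 2 × 2 crossover, "a sample size of 30 participants would provide a power of 90" percent "to demonstrate a 30% reduction in the rate of IDH under the biofeedback treatment vs. the control treatment", "with a two-sided alpha of 0.05". The supporting simulations used "two Poisson processes with average rates of IDH equal to 7 (control) and 5 (intervention) episodes over 24 runs".

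Nowhere does the article state a null ratio of 1.

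**The concern.** The two sections describe different tests. The reduction the investigators hoped to detect appears to have been moved into the analysis section as the edge of the null. To reject a null that extends down to 0.7, the data must show that the ratio is below 0.7, not merely below 1. In confidence-interval terms, the upper 95% limit has to fall under 0.70.

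The sentence also fails on its own terms. The alternative is labelled two-sided but covers one direction only. A ratio above 1.3, which would mean harm, falls under neither hypothesis, and a ratio of exactly 0.7 falls under both. A lesser point is that the band is not symmetric on the log scale on which Poisson regression works, since 1/0.7 = 1.43 rather than 1.3. That does not affect the figures below.

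At stake is the primary conclusion. The same data could be called a success under the sample size section and a failure under the analysis section, and the choice would be open after the results are known.

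**Working it through.** **Inputs** (protocol article)
- Mean episodes per participant over 24 runs: 7 control, 5 intervention. Ratio 5/7 = 0.714, a 28.6% reduction (Sample size calculation).
- Effect in words: 30% reduction, ratio 0.70, or 7 versus 4.9 episodes (Sample size calculation).
- 30 participants, each contributing both periods; two-sided alpha 0.05; stated power 90% (Sample size calculation).
- Null as written: ratio between 0.7 and 1.3 (Statistical analysis).

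**Formula.** Each participant contributes to both treatments, so the subject effect cancels. With Poisson counts,

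SE(log ratio) = √(1/(30 × 7) + 1/(30 × 5)) = √(1/210 + 1/150) = 0.107.

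The chance of rejecting in the lower tail against a null value r0, when the true ratio is r, is Φ[(log r0 − log r)/SE − 1.96].

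**Step 1: reproduce the plan's 90% (r0 = 1)**
- At 0.714: log(1.4)/0.107 = 3.15; Φ(3.15 − 1.96) = 88%. Simulation with 20,000 trials gives 88.5%, or 88.7% with a subject random effect of log-variance 0.2 (an assumed value).
- At 0.70: SE = √(1/210 + 1/147) = 0.1075; Φ(0.357/0.1075 − 1.96) = 91%.
- At 7 versus 5 with at most one episode per run (binomial, 24 runs): 91.6% by simulation.
- Participants needed for 90% power: 31.8 at 0.714 and 28.7 at 0.70, against the stated 30.

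The stated power is therefore that of a two-sided test of ratio = 1. A one-sided 5% test would give 93.4% at 0.714, which fits less well.

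**Step 2: the null as written (r0 = 0.7, its lower edge)**

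At 0.714: (log 0.7 − log 0.714)/0.107 = −0.19; Φ(−0.19 − 1.96) = 1.6%. Simulation gives 1.65%.

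| True ratio | Chance of rejecting, n = 30 |
|---|---|
| 0.714 | 1.6% |
| 0.70 | 2.5% |
| 0.60 | 28% |
| 0.50 | 80% |
| 0.47 | 90% |

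More participants do not help at the design effect: the chance at 0.714 is 1.7% with 24, 1.6% with 30 and 1.5% with 34. The true ratio lies inside the null, so added precision makes rejection less likely.

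**Step 3: what the trial would conclude**
- With 210 control episodes, the observed ratio must be below about 0.82 to reject a ratio of 1, but below about 0.56 to reject the interval null.
- If the trial observes exactly 210 versus 150 episodes, the ratio is 0.714 with 95% interval 0.714 × exp(±1.96 × 0.107) = 0.58 to 0.88. That rejects a ratio of 1 (p about 0.002). It does not reject the null as written, because 0.88 exceeds 0.70.

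**Step 4: gentler readings**
- One-sided 5% test at the 0.7 edge: Φ(−0.19 − 1.645), about 3% at 0.714.
- Success defined as a point estimate of 0.7 or lower: Φ(−0.19), about 43% at 0.714. This is still far from 90%, and it is not a significance test.

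**The case against.** The strongest reply is that this is a slip of wording. The closing paragraph of the Background asks whether biofeedback reduces symptomatic IDH compared with best practice, which is plain superiority. The power figure is correct for that question. The analysis section specifies a model but no confidence-limit rule, and the routine test of the intervention coefficient is against a ratio of 1. The requirement that the upper limit fall below 0.70 is therefore my inference from the literal null. That is fair, and the 1.6% and 2.5% figures describe the literal reading. But the sentence is the article's only statement of the primary hypothesis. An unseen analysis plan can supply what is absent here, but it does not make a hypothesis that is stated wrongly correct.

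It can also be said that the verbal effect, 0.70, is named in the alternative, and that only the whole-number means put 0.714 inside the null. This is true, but it gains little: at the boundary the chance of rejection is 2.5%.

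Failing to reject a null that contains the true ratio is, strictly, no error. The harm comes when that result is read as no effect.

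Finally, the figures at 0.60, 0.50 and 0.47 depend on pure Poisson counts, 7 control episodes and 30 completers. Eligibility requires IDH in more than 30% of sessions (above 0.30 × 24 = 7.2 sessions), and the plan itself allows for over-dispersion, so those figures are illustrative. The result at the design effect does not depend on these inputs: a valid test with 2.5% in the lower tail cannot reject more than 2.5% of the time when the true ratio is at or inside the null's edge.

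A deliberate minimum-effect test is conceivable, but then the sample size would be unsupported. On either reading, one of the two sections has to change.

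**Conclusion.** The concern holds. The primary null as written contains the effect used to size the trial. The 90% power belongs to a different test, that of a ratio of 1, for which it is sound (88% to 92% across reasonable readings). Under the written null, the chance of a positive primary result at the planned effect is 2.5% or less.

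These figures assume 30 completers, the plan's own Poisson means and a conventional 2.5% lower tail. The contradiction between the two sections does not depend on those assumptions. Confusion of the target effect with the null boundary is the likeliest cause, but the text must be corrected because it governs the primary conclusion.

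**What to change.** Replace the hypothesis sentence in Statistical analysis with: null hypothesis, rate ratio = 1; alternative, rate ratio not equal to 1; two-sided alpha 0.05; the rate ratio to be reported with its 95% confidence interval. Keep 0.7 only as the planning effect or as a reference for clinical importance when the interval is read. Harm is then covered by the two-sided alternative, and the analysis agrees with the sample size section.

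The cost is one sentence, with no extra participants or data. The sponsor should confirm before the data are seen that superiority over a ratio of 1 was the intention. If a minimum-effect test was really meant, the sample size has to be redone for a true ratio clearly below 0.7, because no enrolment gives useful power at 0.70 or 0.714.

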### Weight adjustments

Each week participants will have their target weight assessed by a single study investigator (KL). The rounding dialysis physician will be encouraged to discuss any weight adjustments with study personnel.

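### The primary model for this two-period crossover names no period effect, so a drift in IDH between phases biases the rate ratio when the two sequences contribute unequally

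*Protocol article*

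**What the plan says.** **Design.** Under Study design, randomised participants spend 8 weeks on control or biofeedback. "This will be followed by a 2-week washout phase and then the participants will be crossed over for a second 8-week phase". Phase 1 is therefore weeks 5 to 12 and phase 2 weeks 15 to 22.

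**Primary model.** The Statistical analysis section chooses mixed-effects Poisson regression. On fixed effects it says: "We will study the effect of the intervention as a fixed effect". On random effects it says it will "account for the correlation in the data due to the subject using random effects". For over-dispersed data, "we will use a negative binomial regression with the approach as described above". No term for period, sequence or carryover is named in that section or elsewhere in the article.

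**Allocation.** "Randomization of allocation sequence will be done using computer-generated random numbers", under a statistician's supervision and with sealed envelopes. The text is silent on whether the list is blocked.

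**Attrition.** The sample size section enrols 34 and allows that dropout may reach 30%. Participants who leave the city, or move to a unit without the study machine, are censored.

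**The concern.** In a two-period crossover each participant is compared with himself or herself at another time, so a treatment contrast without a period term is also partly a time contrast. When the two sequences are the same size, the time component cancels. When they are not, a remainder stays in the treatment effect.

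Several features of this protocol make a drift plausible:

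- Participants are selected twice on a high IDH frequency, before enrolment and again in the run-in.
- "Each week participants will have their target weight assessed by a single study investigator", and the critical blood volume is also reviewed weekly.
- The outcome depends on symptoms recorded by unblinded nurses, whose recording habits may change over five months.

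Unequal contributions are also plausible. The trial is small, and anyone lost after phase 1 supplies one period only. At stake are the primary rate ratio in the trial actually run and the type I error of its test.

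**Working it through.** **1. Inputs from the protocol.** 30 participants; 7 (control) and 5 (intervention) episodes over 24 runs; two-sided alpha 0.05; 34 enrolled; dropout up to 30%.

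**Assumed, because the protocol gives no value.** The ratio g of the phase 2 rate to the phase 1 rate, taken as 0.9, 0.8 and 0.7, and the split between sequences.

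**2. The plan's own figure.** The sample size section says "a sample size of 30 participants would provide a power of 90% to demonstrate a 30% reduction in the rate of IDH", "with a two-sided alpha of 0.05". For a within-subject Poisson log rate ratio:

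- SE = sqrt(1/(30×7) + 1/(30×5)) = sqrt(1/210 + 1/150) = 0.107.
- Power at 7 versus 5: Φ(ln(7/5)/0.1069 − 1.96) = Φ(1.19) = 88.2%.
- Power at an exact 30% reduction, 7 versus 4.9: 91.3%.

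The stated 90% lies between these, so it reproduces. The calculation mentions no period effect.

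**3. Bias without a period term.** Let a participants receive the intervention first and b receive control first, all with both periods complete. Intervention episodes are proportional to a + b·g and control episodes to a·g + b. The estimated ratio is then

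true ratio × (a + b·g) / (a·g + b).

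If a = b, or if g = 1, the factor is exactly 1.

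| g | Factor, 18 intervention-first : 12 control-first | A true 0.714 reads | Factor with 12:18 | A true 0.714 reads | Log bias in SEs |
|---|---|---|---|---|---|
| 0.9 | 28.8/28.2 = 1.021 | 0.729 | 0.979 | 0.699 | 0.20 |
| 0.8 | 27.6/26.4 = 1.045 | 0.747 | 0.957 | 0.683 | 0.42 |
| 0.7 | 26.4/24.6 = 1.073 | 0.767 | 0.932 | 0.666 | 0.66 |

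With falling rates, an excess of intervention-first participants hides benefit, and an excess of control-first participants creates or exaggerates it.

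**4. Balance at randomisation does not guarantee balance in the analysis.** A list split 17:17 that loses 3 from one sequence and 7 from the other leaves 14:10, or 24 participants. This is close to 34 × 0.7 = 23.8, the number left at 30% dropout. The factors are then 1.018, 1.038 and 1.061 for g = 0.9, 0.8 and 0.7.

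**5. Effect on the test.** Simulation used 40,000 trials per setting, complete pairs, a subject log-SD of 0.4 (assumed) and a null ratio of 1.

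| Setting | Type I error, no period term | Type I error, with period |
|---|---|---|
| 18:12 intervention-first, g = 0.8 | 7.4% | 4.8% |
| 18:12 intervention-first, g = 0.7 | 10.8% | 4.9% |
| Unrestricted splits of 30, g = 0.8 | 7.1% | 5.1% |
| Unrestricted splits of 30, g = 0.7 | 10.2% | 5.0% |

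Over unrestricted splits the mean estimate under the null is 1.000 without the term, so the bias averages out and the error rate does not. At 18:12 intervention-first with g = 0.7 and a true ratio of 0.714, the model without period reads 0.766 with 63% power. With period it reads 0.712 with 80% power.

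**6. Cost of the term when there is no drift.** Estimating the ratio within each sequence and averaging the two logs cancels g. The variance is ¼(1/7 + 1/5)(1/a + 1/b).

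- 15:15: SE 0.107, power 88.2%, so no cost.
- 18:12: SE = sqrt(¼ × 0.3429 × 0.1389) = 0.109, power 86.9%. Simulation gives 88.7% without the term and 87.1% with it.
- Over unrestricted splits: 88.3% without, 86.9% with.
- 20:10: simulation gives 88.2% without and 83.9% with. This more extreme split costs about 4 points.

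**The case against.** **The article does not say that treatment is the only fixed effect.** The model is described in one paragraph, and an analysis plan not shown here may add period. That stands as a limit: a reader might infer that period was deliberately excluded, and the text does not show that. But the section does more than leave the model open. It sets out fixed effect, random effect, error structure and fallback for a crossover, and followed as written it contains no period effect.

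**A drift is not established.** This also stands. A reader might infer that a trend is to be expected, or that target weight changes every week. The protocol says only that weight is assessed weekly, in both phases. The planned dry-weight reduction and both selection windows come before phase 1, so much of the regression to the mean and the early weight change should be over by then. Blood volume monitoring is enabled in the run-in and nurses receive in-service training, so some learning comes earlier too. A drift between phases remains plausible, with its size unknown.

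**Unequal sequences are not established.** A reader might infer unblocked allocation and cite the chance of a split of 18:12 or worse among 30 (36%) or 20:10 or worse (10%). Computer-generated allocation is compatible with blocking, and those probabilities are two-sided: half of each, about 18% and 5%, favours a given sequence. Even so, dropout can unbalance a blocked list.

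**The bias has no fixed direction.** A reader might infer that the plan favours the intervention. It does not: the sign follows the larger sequence.

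**Conclusion.** The point holds as a conditional one. As described, the primary model and its fallback leave the rate ratio open to a phase-to-phase drift whenever the sequences contribute unequally. At 18:12 the shift is at most about two thirds of a standard error over the range of drifts considered. This is modest for the estimate, but enough to take a nominal 5% test to about 7% or 10% at falls of 20% or 30%.

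These sizes rest on assumed drifts, assumed splits, complete pairs and equal dialysis time per period. The figures averaged over splits also assume unrestricted allocation, which the article does not state. The error rates are for a null ratio of 1, not for the range of 0.7 to 1.3 that the Statistical analysis section gives as its null. No figure stated in the plan is shown to be wrong by this point.

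**What to change.** Add period (phase 1 versus phase 2) as a fixed effect in the primary mixed-effects Poisson model and, in the same words, in the negative binomial fallback. Record this before unblinding, so that the term is not chosen after a drift has been seen. If the unshown analysis plan already contains it, cite that and align the article's description.

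The cost is one degree of freedom and no new data. If there is no drift, the power loss is nil with equal sequences, about 1 to 2 points at 18:12 or averaged over unrestricted splits, and about 4 points at 20:10.

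Whether the allocation list is blocked is a separate detail. This fix does not need it, and changing the list would not be simple now that the Trial status section reports enrolment under way.
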